## Discussion

This study will provide the initial evidence of the equivalence of the mobile-based counseling application in improving the CSE and resilience as well as decreasing the level of depression among students with academic problems during the pandemic. While academic distress during the pandemic is the main focus of this study, the application is designed to be relevant to a broad range of mild psychological issues among young people.

The protocol modifications will be communicated after this study is performed. A trial registry amendment will be performed at the TCTR website. Since there was a limited study that tests the equivalency of a protocol in psychological intervention in Indonesia, this study would provide a standardized protocol for improving psychological aspects (i.e., the primary and secondary outcomes) among the students. Furthermore, this study would be very useful in helping people in this pandemic because it provides a protocol that requires no face-to-face condition to deliver counseling sessions.

There were several previous non-inferiority studies in the fields of online psychological intervention. The most common one is cognitive behavior therapy (CBT)-based interventions. Several studies show that the online CBT-based interventions are equivalent to the face-to-face CBT-based intervention with moderate to large effect size in helping participants to reduce insomnia and depression symptoms (Andersson et al., 2013; Wagner et al., 2014; Blom et al., 2015). Norwood et al. (2018) conducted a meta-analysis study regarding the non-inferiority trials on videoconferencing psychotherapy. The study shows that the videoconferencing psychotherapy is partly non-inferior while compared to the face-to-face psychotherapy. Moreover, a study was conducted by Mak et al. (2018) on the efficacy of a mobile application-based program on mental health. The application consisted of (1) mindfulness-based training; (2) self-compassion training; and (3) cognitive-behavioral psychoeducation. This study shows that the application-based program is efficacious in improving well-being. However, this study does not take the non-inferiority margin as a criterion to analyze the non-inferiority of treatment. As a result, this proposed study will enrich the non-inferiority evidence of the online-based SFBT.

As mentioned earlier that this kind of trial needs to have a large number of participants to ensure that the statistical power is sufficient to differentiate the two groups (Hahn, 2012). This study might be able to have the ideal number of participants due to limited resources. However, since the application-based counseling is assumed to be more practical for the young generation, based on the previous studies, we aimed for a small effect size, so the number of participants in this study might be limited but not underpowered.

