## Materials and Methods

### Study Design

This study describes a study that will be conducted as a two-armed parallel randomized controlled non-inferiority trial. The trial is in line with the guidelines for the protocol content of the non-inferiority trial (Piaggio et al., 2012). It will also be based on the guidance of the Standard Protocol Items: Recommendations for Intervention Trials (SPIRIT) Statement (Tetzlaff et al., 2012; Chan et al., 2013). The non-inferiority scheme will be used in this study because the application is not aimed to be more powerful or effective than the usual treatment but aimed to increase the practicality of the counselors to store the data in the application and to hide personal contacts (e.g., email addresses or online meeting IDs) by solely using the application only for the counseling purposes (Hahn, 2012).

To eliminate the assay sensitivity, bias, and constancy assumption (ABC) of this non-inferiority trial, there are several things included in the design. First, the outcome measurement tools that will be used in both groups are reliable. Second, besides using randomizing in allocation and double-blinding procedure, the control group will get the TAU without any intervention to prevent a bias. Third, the data will be collected in the same period for both groups to minimize any situational effects, such as the COVID-19 pandemic-related government policies in this country (Walker, 2019).

The proposed study will be a parallel group design comparing two types of treatments. The intervention group will use the application whereas the control group will get the TAU. The intervention group will have three counseling sessions for a month; meanwhile, the control group will have many sessions based on the need of each individual. All outcomes will be assessed repeatedly using online self-reported forms, which will be facilitated by research assistants. The assessments will be taken (1) before the intervention, (2) after each session (a session/week), and (3) after 3 months. The study design is shown in Figure 1.

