### Participants

The target population in the study will be University students who have academic-related psychological problems. The inclusion criteria of the sample are a University student, aged 18–25 years old, having academic-related problem(s), and registering as a participant in this study. The academic-related problems that will be included in the study are (1) (educational) adjustment difficulties; (2) difficulties in writing a thesis; (3) academic procrastination; (4) poor self-regulation for learning; and (5) a low grade point average (GPA). The study will exclude students with (1) physical disabilities; (2) under the care of mental health professionals; and (3) the score of PHQ-9 more than 14 (having severe depression), (Rahmadiana et al., 2019).

The participants of the study will be those who register in a University counseling center. They will be then screened with the PHQ-9. If they are willing to participate in the study, the research assistants will give informed consent and the right to withdraw from the study at any given time they wish to. The students who decline to join the study or withdraw from the study will be followed up to identify their reasons for declining and withdrawing from the study. The students have a right to undergo post-trial treatment if needed.

The sample size is a sensitive issue in the non-inferiority trial (Hahn, 2012). Large sample size is usually needed. However, if the new intervention is assumed to be slightly more effective than the TAU, the number of samples can be reduced. The mobile-based counseling application can be assumed to be more practical for the students in this country. Those who live remotely can still access the psychological services. The data from the University counseling center in 2020 were also a source of consideration in determining the sample size. The center admitted 482 clients in that year, with an average of 40 clients per month. With 80% CI, the expected SD will be one, and the inferiority margin (Δ) will be 0.24. It was calculated that the number of participants per arm needs to be 215 and the total sample size needs to be 430.

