### Determining an Inferiority Margin of the Trial

In the non-inferiority trial, the researchers need to determine Δ (Hahn, 2012). In this study, the margin is the maximum acceptable extent of non-inferiority of the mobile-based counseling application. The maximum limit of Δ can be set to the entire effect size of the active control treatment (Hahn, 2012). Several proposals for choosing the inferiority margins in the context of SFBT have been made (Table 1). There are several suggestions for the maximum difference in outcomes that will be considered clinically irrelevant. It ranges from *d* = 0.17 to *d* = 1.76. The smallest margin was suggested by Schmit et al. (2016), (*d* = 0.24) for the treatment of internalizing disorders. Thus, in this study, it was decided to use the inferior margin of 0.22 (i.e., the inferior margin up to 0.22), corresponding to a small effect size.

**Table 1 T1:** The effect size from the solution-focused brief therapy (SFBT)-related studies.

**Previous studies**	**Effect size**
Impacts on academic and emotional difficulties (Daki and Savage, 2010)	≈0.13 (partial eta squared, medium effect size)
Meta-analysis of solution-focused brief therapy for treating symptoms of internalizing disorders (Schmit et al., 2016)	≈0.24 (Hedges' g, small effect size)
Examining the effectiveness of solution-focused brief therapy: a meta-analysis (Kim, 2008)	0.26–0.38 (Cohen's *d*, small effect size)
SFBT for health-related psychosocial outcomes (Zhang et al., 2018)	0.34 (Cohen's *d*, small effect size)
Solution-focused brief therapy in schools: A review of the outcome literature (Kim and Franklin, 2009)	0.38–1.76 (Cohen's *d*, medium to large effect size)

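### The claim that limited numbers would still be adequately powered is unsupported: under the stated 95% interval and no true difference, even the full 430 gives about 70% or 63% power

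*Protocol article*

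**What the plan says.** The Discussion acknowledges that non-inferiority trials need many participants and mentions limited resources. It then argues from the application's practicality for young people and from a small target effect size to the conclusion: "so the number of participants in this study might be limited but not underpowered".

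The same idea appears in Participants: "if the new intervention is assumed to be slightly more effective than the TAU, the number of samples can be reduced". The next sentences offer practicality and access for students living remotely, and give no figure for greater effectiveness. Study Design says that "the application is not aimed to be more powerful or effective than the usual treatment".

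The sizing inputs in Participants are: "With 80% CI, the expected SD will be one, and the inferiority margin (Δ) will be 0.24". They lead to 215 per arm and 430 in total. No significance level and no true difference are given there. Determining an Inferiority Margin of the Trial settles on another value: "it was decided to use the inferior margin of 0.22 (i.e., the inferior margin up to 0.22". Data Analysis tests non-inferiority with a 95% confidence interval using 1.96, and concludes it when the upper limit of the treatment difference is below the margin.

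**The concern.** The Discussion sentence asserts a power property, and the reasons given for it do not lead there.

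- **Small effect size.** In a non-inferiority comparison the required number per arm is proportional to 1/Δ². Aiming for a small margin raises the number needed.
- **Practicality.** Only a true advantage on the outcome being tested can reduce the sample size. Ease of use and remote access are not such an advantage, and the article gives no figure for one.
- **The design's stated purpose.** Study Design says the application is not meant to outperform usual treatment, which sits badly with a reduction that depends on its being slightly better.

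At stake is how a failed result is read. If the trial is described in advance as adequately powered, a result that misses the margin may be taken as evidence against the application when the interval was simply too wide. The decision rule in Data Analysis adds to this risk. It names an outcome for an interval wholly above the margin and one for an upper limit below it, but none for an interval that spans it.

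**Working it through.** **Inputs.** SD 1, margin 0.24 and 215 per arm come from Participants. Margin 0.22 comes from the margin section. The 95% interval with z = 1.96 (one-sided 2.5%) comes from Data Analysis. Two inputs are assumptions: the 80% in Participants, attached there to a confidence interval, is read as 80% power; and the true difference is taken as 0 because no value is given.

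**Step 1: reproduce 215.** With equal arms and no true difference,

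n per arm = 2·SD²·(z₁₋α + z_power)² / Δ².

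- One-sided 5%, Δ = 0.24: 2 × (1.6449 + 0.8416)² / 0.24² = 12.365 / 0.0576 = 214.7, so 215 per arm and 430 in total. This matches the article.
- At 214 per arm, power is already 79.9%. On this calculation there is no reserve.

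**Step 2: apply the rule in Data Analysis.** With z = 1.96 and 80% power,

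- Δ = 0.24: 2 × (1.96 + 0.8416)² / 0.0576 = 15.698 / 0.0576 = 272.5, so 273 per arm (546 in total);
- Δ = 0.22: 15.698 / 0.0484 = 324.3, so 325 per arm (650 in total).

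Neither is 215. The move from 0.24 to 0.22 alone multiplies the requirement by (0.24/0.22)² = 1.19, which shows the direction in which a smaller margin works.

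**Step 3: power at the planned and at lower numbers.**

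Power = Φ(Δ·√(n/2) − z), with SD 1 and true difference 0.

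For n = 215, √(215/2) = 10.368. At Δ = 0.24: 2.488 − 1.960 = 0.528, Φ = 70.1%. At Δ = 0.22: 2.281 − 1.960 = 0.321, Φ = 62.6%.

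| Total | Per arm | Δ 0.24, z = 1.645 (level not stated) | Δ 0.24, z = 1.96 | Δ 0.22, z = 1.96 |
|---|---|---|---|---|
| 430 | 215 | 80.1% | 70.1% | 62.6% |
| 344 | 172 | 71.9% | 60.5% | 53.2% |
| 300 | 150 | 66.8% | 54.7% | 47.8% |

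The totals of 344 (20% short) and 300 are illustrations and are not in the article.

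**Step 4: is the reproduction in Step 1 unique?** It is not. Other settings give the same number:

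- z = 1.96, Δ = 0.24, 80% power and a true advantage of 0.03 SD: 15.698 / 0.27² = 215.3;
- one-sided 5%, Δ = 0.22 and a true advantage of 0.02 SD: the effective distance is again 0.24, so 215;
- one-sided 20% with 95% power, Δ = 0.24 and no true difference: 215, because the formula is symmetric in the two z-values.

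The article states none of these combinations.

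**The case against.** The strongest reply is that power depends on the true difference, and Participants does raise the possibility of a small advantage. With a true advantage of 0.05 SD, the full 430 under the 95% interval would have 85.2% power at margin 0.24 and 79.9% at 0.22. That arithmetic stands. But the article gives no value for an advantage and offers practicality in its place, so the claim cannot rest on it.

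It can also be said that the wording is ambiguous. The Discussion sentence just before the claim is garbled, and limited may describe 430 itself against the large samples usual in such trials. This also stands. The claim is unsupported on either reading.

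Four stronger readings are tempting, and the documents do not support them:

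- **That 430 is exactly enough and only a recruitment shortfall would take power below 80%.** This needs a one-sided 5% level that the article never states. Under its stated interval and a true difference of 0, power is below 80% at full enrolment.
- **That 215 proves no reduction was taken for an assumed advantage.** Step 4 shows that small advantages give about the same number, so the article does not settle this.
- **That the article permits stopping short of 430.** No passage does so.
- **That the intake makes 430 unattainable.** Participants says "The center admitted 482 clients in that year, with an average of 40 clients per month", and 430/482 is 89% of one year's clients. But the article states no recruitment period and no eligible or consenting fraction, so this shows nothing about feasibility.

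**Conclusion.** The concern holds in this form: the article's own figures do not support its statement that limited numbers would not be underpowered. Under the analysis it describes (95% interval, z = 1.96), with SD 1 and no true difference, 430 participants give about 70% power at margin 0.24 or 63% at margin 0.22. Lower enrolment reduces this to about 60% or 53% at 344, and 55% or 48% at 300.

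The 80% benchmark is itself a reading of an unclear phrase, and a real advantage for the application would raise every figure. Nothing here shows which margin, level or true difference the investigators had in mind. The article gives two margins and, on the simplest reproduction, two levels, and it claims adequate power without a set of inputs that delivers it.

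**What to change.** 1. In the Discussion, delete the statement that the trial would not be underpowered.
2. In Participants, delete the argument that the sample can be reduced, or state the assumed true difference as a number with its basis. If it is zero, say so.
3. Reconcile the margin (0.24 in Participants, 0.22 in the margin section) and the confidence level (sizing against the 95% interval in Data Analysis). State plainly what the 80% refers to.
4. Restate the power that 430 delivers under the reconciled rule, and the power at one or two lower enrolments. The 71.9% and 66.8% in the one-sided 5% column should not be printed while the analysis uses a 95% interval.
5. Say how an interval that spans the margin will be reported.

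Suggested wording, to be completed after step 3: *The sample size assumes a true difference of [value] SD, a margin of [value] SD and a [level] confidence interval. Under these assumptions 430 participants give [x]% power; [lower number] would give [y]%. If non-inferiority is not shown and the interval spans the margin, the result will be reported as inconclusive.*

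The correction needs a short recalculation and changes of wording, and no extra participants. Its downside is a less favourable stated power. Whether to enlarge the trial in response is a separate decision.

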## Ethics Statement

The studies including human participants were reviewed and approved by the Research Ethics Committee of Universitas Padjadjaran, Indonesia (No.1455/UN6.KEP/EC/2019) and has been registered in Thailand Clinical Trials Registry (Identifier: 94 TCTR20200530001). Protocol amendments will be updated in the trial registry (TCTR). Participants will provide their written informed consent to participate in the study.

## Abbreviations

RCT: randomized control trial
CSE: Coping Self-Efficacy
RS: Resilience Scale
TCTR: Thailand Clinical Trials Registry
SPIRIT: Standard Protocol Items: Recommendations for Intervention Trials
TAU: Treatment-As-Usual
PHQ: Patient Health Questionnaire
SFBT: solution-focused brief therapy
CBT: cognitive behavioral therapy
REBT: rational emotive behavior therapy.
